#### **Efficacy Analysis:**

All treated subjects will be included for efficacy analysis. Efficacy will be analyzed once all subjects have withdrawn from the study or completed at least 6 cycles. The hypothesis test for the objective confirmed response rate will be based on the exact binomial distribution for the Phase 2b – Expansion part. Ninety-five percent confidence intervals will be provided. A case-by-case description of all subjects who exhibited a complete or partial response during the study will be provided. A descriptive analysis of other evidence of anti-tumor activity will be provided based on clinical, radiographic, and biologic assessments of efficacy. If there are sufficient data, Kaplan-Meier estimates will be provided for duration of response, PFS, DCR, and OS.

Data listings will be provided for all relevant data collected during the studies.

**Table 2: Table of Assessments**

| Assessments                                       | Screening Period                                    | Treatment Period (28 Day Treatment Cycle) |                                | Follow-Up Period                     |                                             |
|---------------------------------------------------|-----------------------------------------------------|-------------------------------------------|--------------------------------|--------------------------------------|---------------------------------------------|
|                                                   | -28 to -1                                           | Every Cycle Day 1 (Pre-dose)  | Discontinuation from Treatment | 28 Days After Last Dose (+/- 3 days) | Every 90 Days After Last Dose (+/- 14 days) |
| Entry Assessments                     |                                                     |                                           |                                |                                      |                                             |
| Informed Consent                                  | X                                                   |                                           |                                |                                      |                                             |
| Inclusion/Exclusion Criteria                      | X                                                   |                                           |                                |                                      |                                             |
| Complete Medical History                          | X                                                   |                                           |                                |                                      |                                             |
| Prior Therapies                       | X                                                   |                                           |                                |                                      |                                             |
| Safety Assessments                                |                                                     |                                           |                                |                                      |                                             |
| Adverse Event Query                               | After signing ICF and until 28 days after last dose |                                           |                                |                                      |                                             |
| Physical Examination                  | X                                                   | X                                         | X                              | X                                    |                                             |
| Vital Signs                           | X                                                   | X                                         | X                              | X                                    |                                             |
| Height                                            | X                                                   |                                           |                                |                                      |                                             |
| Weight/BSA                            | X                                                   | X                                         | X                              | X                                    |                                             |
| Hematology Labs                       | X                                                   | X                                         | X                              | X                                    |                                             |
| Serum Chemistry Labs                  | X                                                   | X                                         | X                              | X                                    |                                             |
| Thyroid Function Tests                | X                                                   |                                           | X                              |                                      |                                             |
| Pregnancy Test                        | X                                                   | X                                         | X                              | X                                    |                                             |
| Concomitant Medications/
Procedures            | After signing ICF and until 28 days after last dose |                                           |                                |                                      |                                             |
| Efficacy Assessments                              |                                                     |                                           |                                |                                      |                                             |
| ECOG Performance Status                           | X                                                   | X                                         | X                              |                                      |                                             |
| Tumor Assessments                    | X                                                   | X                            | X                 |                                      |                                             |
| Response Assessments                              |                                                     | X                            | X                 |                                      |                                             |
| Survival                             |                                                     |                                           |                                |                                      | X                                           |
| Exploratory Assessments                           |                                                     |                                           |                                |                                      |                                             |
| Blood for Biomarker                               |                                                     | X                            | X                 |                                      |                                             |
| Tumor for Biomarker                               | X                                      |                                           |                                |                                      |                                             |
| Investigational Product                           |                                                     |                                           |                                |                                      |                                             |
| Dispense Investigational Product(s)  |                                                     | X                                         |                                |                                      |                                             |
| Drug Accountability                  |                                                     | X                                         | X                              |                                      |                                             |

-  Screening assessments completed within 14 days prior to Cycle 1 Day 1 need not be repeated at Cycle 1 Day 1. Assessments may be done up to 3 days prior to Day 1 for all other cycles. During Cycle 1, visits will occur every 7 days to assess physical examination, vital signs, haematology laboratory evaluations, and serum chemistry laboratory evaluations. Paraffin tumor blocks or approximately 25 unstained slides must be sent for KRAS mutant testing and status reported by central pathology lab prior to study enrollment.
-  All prior radiotherapy, relevant surgeries, and chemotherapies and approximate dates of therapies must be recorded.

### **Safety Assessments**

-  A complete physical exam is required. The Investigator should describe/capture any abnormal findings. Occurs every 7 days during Cycle 1.
-  Vital signs include pulse, blood pressure, and temperature. Occurs every 7 days during Cycle 1.
-  The dose of chemotherapy does not need to be changed unless the calculated dose, according to BSA changes by  $\geq 10\%$ .
-  Hematology: RBC count, hemoglobin, hematocrit, WBC count and differential (including ANC) and platelet count. Occurs every 7 days during Cycle 1. May be repeated more frequently if clinically indicated.
-  Serum Chemistry: Sodium, potassium, chloride, CO2, calcium, magnesium, phosphorus, BUN, creatinine, glucose, albumin, total protein, alkaline phosphatase, bilirubin, AST/SGOT, ALT/SGPT, LDH and uric acid. Occurs every 7 days during Cycle 1. Any or all may be repeated more frequently if clinically indicated.
-  Thyroid Stimulating Hormone (TSH) and free T3 and T4 levels will be determined. May be repeated more frequently if clinically indicated.
-  WCBP who participate in the study will have urine  $\beta$ -HCG levels assessed as a means of pregnancy testing. The subject may not receive investigational product(s) until the investigator has verified that the results of these pregnancy tests are negative (see specifics in Section 21.3 or 21.4).

### **Efficacy Assessments**

-  Conventional (or spiral) CT/MRI scans are required. Subjects having received a scan during the Screening Period are not required to have a scan at Cycle 1 Day 1.
-  Conventional (or spiral) CT/MRI scans are required every 2 cycles beginning with Cycle 3 Day 1. Scans must be done within 7 days prior to Day 1 of the cycle. To ensure comparability, baseline methods and on-study methods for tumor assessment must be performed using identical techniques. Chest X-ray may be performed only when clinically indicated.
-  Scan should be performed at treatment discontinuation unless last scan was performed within the prior 28 days.
-  Tumor response will be evaluated every 2 cycles beginning with Cycle 3 Day 1 and at treatment discontinuation. Response and progression will be evaluated using the RECIST 1.1

criteria. All subjects with evidence of objective tumor response (CR and PR) should have the response confirmed at the next scheduled scan (every 2 cycles following Cycle 1 Day 1).

-  Survival data will be captured via phone contact every 90 days until death or 5 years post-discontinuation.

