#### **12.2.1. Tumor Assessment**

Tumor assessment conventional (or spiral) CT, or MRI will be performed at screening, every 2 cycles beginning with Cycle 3 Day 1, and at treatment discontinuation. Subjects who have received screening scans within 28 days of Cycle 1 Day 1 do not need to have an additional scan done. Discontinuation from study scans do not need to be done if last scan was performed within the prior 28 days. During the study, scans must be done up to 7 days prior to Day 1 of the cycle. To ensure comparability, baseline methods and on-study methods for tumor assessment must be performed using identical techniques. X-rays will be performed only when clinically indicated.

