#### **12.2.2. Response Assessment**

Tumor response will be evaluated every 2 cycles beginning with Cycle 3 Day 1 and at treatment discontinuation. Response and progression will be evaluated using the RECIST 1.1 criteria ([Eisenhauer, 2009](#)). All subjects with evidence of objective tumor response (CR and PR) should have the response confirmed with repeat assessments performed at the next scheduled scan (every 2 cycles following Day 1 Cycle 1).

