### **15.2. Efficacy Evaluation**

All treated subjects will be included for efficacy analysis. Efficacy will be analyzed once all subjects have withdrawn from the study or completed at least 6 cycles. The hypothesis test for the objective confirmed response rate will be based on the exact binomial distribution Phase 2b – Expansion part. Ninety-five percent confidence intervals will be provided. A descriptive analysis of other evidence of anti-tumor activity will be provided based on clinical, radiographic, and biologic assessments of efficacy. If there are sufficient data, Kaplan-Meier estimates will be provided for duration of response, PFS, DCR, and OS.

Data listings will be provided for all relevant data collected during the studies.

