#### **15.7. Sample Size and Power Considerations**

During Phase 2a – Safety Lead-in part, up to approximately 18 subjects will be enrolled.

In the Phase 2b – POC part, up to approximately 82 subjects will be randomized in a 1:1 ratio between lenalidomide in combination with cetuximab and lenalidomide alone. A Simon two stage minimax design will be used to monitor subject enrollment for each randomization arm separately. In the first stage, 23 subjects will be enrolled. If  $\leq 2$  of the 23 subjects ( $< 10\%$ ) have a response in either arm, the enrollment for that arm will be stopped. If  $> 2$  of the 23 subjects have a response in either arm, the enrollment in that arm will continue until 41 subjects are enrolled. If one arm is stopped, all new subjects will be enrolled in the remaining arm. At the final analysis, the regimen will be concluded with more than 10% true response rate if  $\geq 9$  of 41 subjects ( $>21\%$ ) have a response. This design will have 90% power to conclude the true response rate is higher than 10% at one-sided 2.5% level when the true response rate is 30%.

When any arm from the Phase 2b – POC is considered positive, the study may proceed with that regimen to the Phase 2b –Expansion phase. In the Expansion phase, approximately 120 subjects will be treated with the regimen. This sample size will allow for a two sided 95% confidence interval of (22%, 39%) when 30% response rate is observed.

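### The 6-cycle analysis trigger comes before the scan that would confirm a response first seen at Cycle 7, so the Expansion's confirmed response rate can be biased slightly down

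*Protocol*

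**What the plan says.** - **Scans.** Table 2 (footnotes 11 and 13) and Section 12.2.1 place CT/MRI at Cycle 3 Day 1 and every second cycle after that, each in the 7 days before Day 1. Cycles last 28 days.
- **Confirmation.** Under Section 12.2.2, subjects with a CR or PR "should have the response confirmed with repeat assessments performed at the next scheduled scan (every 2 cycles following Day 1 Cycle 1"). Footnote 13 of Table 2 says the same.
- **End of treatment.** Section 12.2.2 also makes discontinuation a time point for response evaluation. Footnote 12 limits the scan there: "Scan should be performed at treatment discontinuation unless last scan was performed within the prior 28 days". Section 12.2.1 repeats the limit: "Discontinuation from study scans do not need to be done if last scan was performed within the prior 28 days". Table 2 marks no tumor assessment in either follow-up column, and Section 8.4 provides one 28-day visit followed by telephone contacts.
- **Analysis time.** Section 15.2: "Efficacy will be analyzed once all subjects have withdrawn from the study or completed at least 6 cycles". The same section includes all treated subjects and ties the hypothesis test on the confirmed rate to the Expansion. Section 15.6 rests the primary efficacy analysis on Expansion data alone.
- **Proof-of-concept (POC) rule.** Section 15.7 counts subjects with a response, without the word confirmed, and states "90% power to conclude the true response rate is higher than 10% at one-sided 2.5% level when the true response rate is 30" per cent.

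**The concern.** The Expansion's primary endpoint needs two scans per response, one to see it and one to confirm it, and these are two cycles apart. The analysis time in Section 15.2 is set by cycles completed, without regard to whether a confirming scan is pending. If the analysis is run at the earliest moment allowed, some responses already visible in the data will lack the scan that decides whether they count.

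All treated subjects are in the analysis, so unless a rule elsewhere says otherwise such a subject counts as a non-responder. The error runs in one direction: it can understate activity in the part of the trial that carries the primary analysis. It cannot inflate the type I error.

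**Working it through.** **1. Which responses can be confirmed by the 6-cycle minimum**

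Inputs: 28-day cycles, scans at odd-numbered cycles from Cycle 3, and confirmation at the next scheduled scan, which is 2 × 28 = 56 days later (Table 2; Sections 12.2.1 and 12.2.2).

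| First seen at | Cycles completed | Confirming scan | Cycles completed | In hand at 6 cycles? |
|---|---|---|---|---|
| Cycle 3 Day 1 | 2 | Cycle 5 Day 1 | 4 | yes |
| Cycle 5 Day 1 | 4 | Cycle 7 Day 1 | 6 | yes, scan falls in the last week of Cycle 6 |
| Cycle 7 Day 1 | 6 | Cycle 9 Day 1 | 8 | no |

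Six cycles end on day 6 × 28 = 168. Cycle 9 Day 1 is day 8 × 28 + 1 = 225. The wait is at most 225 − 168 = 57 days, about 8 weeks, if cycles run to schedule. Only subjects with little more than the minimum follow-up are affected. Those enrolled earlier will already have had the Cycle 9 scan.

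**2. What one such response is worth in the Expansion**

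Section 15.7 plans about 120 subjects and illustrates a 30% observed rate, so 0.30 × 120 = 36 responders. The exact 95% interval for 36/120 is 22.0% to 39.0%, which reproduces the stated (22%, 39%). Each response left unconfirmed lowers the rate by 1/120 = 0.83 percentage points, for example from 36/120 = 30.0% to 35/120 = 29.2%. The half-width of the stated interval is (39 − 22)/2 = 8.5 points. The protocol does not say how many responses would first appear at Cycle 7 in late-enrolled subjects.

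**3. Stopping treatment before the confirming scan**

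Take a subject with a first CR or PR who stops without progression:

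- Stop within 28 days of that scan: the discontinuation scan is waived and none follows.
- Stop after 28 days but before the next scheduled scan at about 56 days: a discontinuation scan is done and response is evaluated, but the text does not say whether this can serve as the next scheduled scan for confirmation.

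In the first case the response cannot be confirmed under the schedule. In the second its status is undefined.

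**4. The POC power figure**

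Inputs from Section 15.7: stop an arm if at most 2 of 23 respond, succeed if at least 9 of 41 respond, null rate 10%, alternative 30%. With X ~ Bin(23, p) and Y ~ Bin(18, p),

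P(success) = Σ over x = 3 to 23 of P(X = x) · P(Y ≥ 9 − x).

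- p = 0.30: 0.902, the stated 90%.
- p = 0.10: 0.018, within the stated one-sided 2.5%.

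If a share f of responders were lost across all subjects, p becomes 0.30 × (1 − f):

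- f = 5% (assumed): p = 0.285, power 86.2%.
- f = 10% (assumed): p = 0.27, power 81.0%.

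A cut-off effect would touch only late-enrolled subjects. With 10% of responders lost among the last 5 subjects, power is 89.4%; among the last 10, it is 88.5%. All of these reduced figures also need two premises that Section 15.7 does not state, namely that POC responses must be confirmed and that 30% is a rate before confirmation.

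**The case against.** The case for leaving the text alone has several parts.

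- **Six cycles is a minimum.** It lets responses from the first two scans be confirmed, and the sponsor may wait longer. This is true and keeps the effect small, but the text permits an analysis at the minimum.
- **A later trigger only moves the edge.** With an 8-cycle trigger, a response first seen at Cycle 9 would be the one left pending. This stands against a later fixed trigger. It does not stand against waiting for confirmations already pending.
- **Pending confirmations are commonly handled in the SAP, which is not shown.** Partly fair, but the analysis time is fixed in the protocol.
- **Counting an unconfirmed response as a non-response is conservative.** True for type I error, but the estimate is still biased low for an avoidable reason.
- **Few subjects stop soon after a first response.** Sections 8.1.2 and 10.3 let lenalidomide continue when cetuximab is discontinued, so scans can go on. Plausible, and the reason why this part is secondary.

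Two stronger readings are tempting. A reader might infer that the POC part loses its stated 90% power. The documents do not support this: the POC rule counts responses without requiring confirmation, the 90% is conditional on a 30% rate of the endpoint as counted, Section 15.2 does not say that its trigger governs the POC stage decisions, and no share of lost responders is given. A reader might also take the 28-day waiver to be the main cause. It drops only a scan close to the previous one, whereas confirmation is due about 8 weeks later, and nothing says that the waived scan would have confirmed anything. The deeper cause is that no tumor scan follows discontinuation.

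**Conclusion.** The point holds in a narrow form. At the earliest analysis time that Section 15.2 allows, a response first seen at Cycle 7 Day 1 in a last-enrolled subject cannot yet be confirmed, so the Expansion's confirmed response rate can be biased slightly down. The size is unknown from the document; each such response costs 0.83 percentage points in 120 subjects. The conclusion assumes that cycles run on schedule, that the analysis is done at the minimum, and that unconfirmed responses count as non-responses.

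Secondarily, a responder who stops without progression before the next scheduled scan may stay unconfirmed, and the protocol does not say whether a discontinuation scan can confirm.

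The POC design delivers 90.2% power at a 30% rate of the endpoint as counted, and that figure stands. This is an inexpensive improvement, not a flaw that undermines the design.

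**What to change.** **Section 15.2.** Keep the 6-cycle minimum, and add that the response-rate analysis is held until every CR or PR first seen by that time has had its next scheduled scan or the subject has left treatment. Responses first seen after that time do not extend the hold. Cost: one sentence, no added scan, and a cut-off later by up to about 8 weeks, only if a confirmation is pending.

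**Table 2 footnote 12 and Sections 12.2.1 and 12.2.2.** Reconcile these on whether a discontinuation scan can confirm a response, and state how a response still unconfirmed at discontinuation is counted. Cost: wording only.
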